Enhancement of social engagement	- Assessment of level of social activity and risk of social isolation - Information on the importance of an active lifestyle including high social engagement for dementia risk - Enhancement of social engagement will be planned together with each study participant individually
Bereavement, grief and depressive symptoms	- Assessment of depressive symptoms and underlying risk factors (e.g. bereavement, grief) - If necessary, participants will be encouraged to contact their GP and will be provided with adequate support and care (e.g. referring participants to groups, psychiatrists, psychotherapists, psychiatric hospitals). Additionally, participants will receive written information on addresses and helplines which can be contacted in case of grief and/or depressive symptoms. - If applicable, encouragement to use MoodGym – a scientifically developed and evaluated free web-based training program to prevent and reduce depressive symptoms (http://www.moodgym-deutschland.de/).
Motivational tasks across all components	- Personnel continuity regarding the contact person for the participants - Study nurses will be trained in motivational interviewing techniques and participants will be strongly encouraged to contact their contact person, whenever necessary - Birthday/Christmas/holiday cards originally signed by trial authorities/principal investigators - Participants of intervention A will receive a brochure including recommendations (additional tips and suggestions each week for an active lifestyle, e.g. recipes, suggestions for physical activity, and information on healthy ageing) as well as a weekly diary to track their activities in the intervention components.

Participants of intervention group B (basic) will receive *GP treatment as usual* (GPTAU) and *general health advice* (GHA) related to the components of intervention A. We hypothesize that the multi-component intervention program of intervention A will be superior to GPTAU and GHA (intervention B) regarding trial outcomes.

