At baseline and at follow-up assessment after 24 months, fully structured interviews will be conducted with all participants, assessing the primary and secondary endpoints. Other relevant information assessed include sociodemographic information, subjective cognitive decline, self-reported impairments and symptoms, anthropometry, blood pressure, nutrition, physical activity, bereavement/grief, medication, vascular risks). Moreover, GPs will provide data on participants’ health characteristics (diagnoses, lab values, medication) using standardized questionnaires. To conduct the process evaluation, the success rate of recruitment (number of eligible GP patients, number of participants and non-participants, (baseline) characteristics of participants and non-participants, reasons for non-participation) will be provided by the GP practice personnel. Standardized telephone interviews on reasons for dropout will be held with intervention A-participants, if applicable. For participants in intervention A, additional interim sessions will be scheduled: one face-to-face assessment after 12 months at the participants’ home and five telephone calls after 2, 4, 8, 16, and 20 months, respectively (see Table 3). These fully structured interviews serve the purpose of monitoring adherence to the intervention and motivation (monitoring & booster sessions). Participants in intervention group A will be asked to track their activities in the intervention components using weekly diaries. To reduce non-response as well as dropout in *AgeWell.de*, interviewers will undergo training regarding all procedures and assessments, including motivational interviewing techniques [64]. Likewise, motivational tasks will also be carried out by the principal investigators (Table 1).

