**Table 3 Tab3:**
[figure not shown]
Schedule of enrolment, interventions and assessments in the course of *AgeWell.de*

^1^: Telephone interim monitoring and booster sessions 2, 4, 8, 16, and 20 months after baseline-assessment in intervention group A; ^2^: Face-to-face intervention visit in intervention group A after 12 months; ^3^: limited assessment of the actual medication via telephone

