### Statistical analyses

Preliminary analyses involve three parts. First, data will be cleaned and checked for inconsistencies by statisticians at the central data management center to ensure data accuracy and coherence. Second, outcome variables will be examined to identify potential outliers and leverage points. Third, missing data will be inspected and handled according to patterns of data missingness, e.g., by multiple imputation [65].

A dropout analysis will be performed to test whether complete and incomplete cases differ according to relevant sociodemographic variables, potentially introducing selection bias.

Descriptive analyses will be carried out to examine differences in baseline measurements regarding the composite cognitive *z-*score (primary endpoint) and secondary endpoints between the two intervention groups. Additionally, single scores for the six neurocognitive domains will be calculated and analyzed. Suitable balancing techniques, such as entropy balancing, will be used for baseline measurements to warrant a high degree of comparability between study groups [66]. In order to analyze changes in primary and secondary endpoints of the two groups over time (treatment effect), latent growth curve modeling (LGM) will be utilized. Group membership (A vs. B) as well as other time-invariant characteristics will be assessed as predictors of change in cognitive performance in the models. Model estimates will be weighted using, for example, calculated entropy balancing weights to equalize possible baseline differences in covariates and outcomes. The models will further be stratified by age and gender to evaluate whether treatment effects on primary and secondary outcomes differ by subgroups.

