### Harms

Trial-related adverse events (AEs) will be assessed without regard towards a causal relation to the intervention. AEs will be recorded at each contact with participants after the baseline assessment. AEs in *AgeWell.de* include loss experiences and grief, depressive symptoms, severe injuries, hospitalization, and private or occupational stress reported by participants. Specific AEs (depressive symptoms; severe injuries; hospitalization) will be considered serious adverse events (SAEs) if they result in a life-threatening condition (immediate risk or death), hospitalization/prolongation thereof, or any lasting impairment. Occurrence of AEs/SAEs will be documented in the electronic database after each contact with participants. In case of a SAE, an automatic case-report form will notify the coordinating study center at the University of Leipzig, which, in turn, will contact the respective study center. A shared decision will then be made between the coordinating study center and non-elective principal investigator (PI) at the respective study center, including one of the following options: informing the participants’ GP about the SAE, interruption or discontinuation of trial participation, or none of the above.

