### Limitations

Participation in our prevention trial is rather demanding since the intervention components address various lifestyle factors and require e.g. cognitive training and physical activity on several days a week. The follow-up period is longer than in most previous trials testing single interventions. Therefore, adherence to the intervention might be lower compared to trials targeting only single components for a shorter time period. These factors also raise the chance of dropping out. We will address these potential problems by putting a strong focus on continuous motivation of participants and monitoring of adherence to the intervention, e.g. by regular telephone contacts and the use of motivational interviewing techniques. For ethical reasons, general health advice and feedback on known risk factors for dementia will also be provided to intervention group B. On these grounds, estimates of the effects of our intervention should be considered to be conservative.

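### After a serious adverse event the only stop listed is of trial participation; any primary-endpoint loss from this would fall mainly on group A, and a short wording change prevents it

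*Protocol article*

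**What the plan says.** Under Harms, the coordinating center and the principal investigator of the site decide together what follows an SAE. The options are to inform the GP, "interruption or discontinuation of trial participation, or none of the above". The same section sets when events are found: "AEs will be recorded at each contact with participants after the baseline assessment".

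Data collection describes the contacts. At baseline and at 24 months, "fully structured interviews will be conducted with all participants, assessing the primary and secondary endpoints". Between those points, interim sessions are described for group A only: a home visit at 12 months and "five telephone calls after 2, 4, 8, 16, and 20 months, respectively". The Table 3 footnotes repeat this, for example "Face-to-face intervention visit in intervention group A after 12 months". Table 1, which describes the group A programme, adds that "participants will be strongly encouraged to contact their contact person, whenever necessary".

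On missing outcomes, Statistical analyses says that "missing data will be inspected and handled according to patterns of data missingness", with multiple imputation as an example.

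**The concern.** The only stop on the list acts on participation in the trial. Nothing in the article says that someone stopped in this way keeps the 24-month assessment, and the cognitive composite is described only at baseline and 24 months. A participant whose follow-up ends after an SAE therefore has no later cognitive score. Imputation would have to rest on baseline and other covariates and could repair the loss only in part.

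The occasion to use the option differs between the arms. In the schedule described, group A has six contacts at which an SAE can come to light before month 24. Group B has none described until the 24-month interview, when the endpoint is itself collected. If the option ends follow-up, and if those removed have worse cognitive courses, the remaining A participants look better than the full A group. That is the direction of the trial's hypothesis.

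**Working it through.** **1. Can the rule remove the endpoint, and in which arm?**

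- Harms: a stop of participation is possible after an SAE, and SAEs are found at contacts.
- Data collection and Table 3 footnotes: contacts for A at months 2, 4, 8, 12, 16 and 20, then 24. For B, month 24 is the first contact described after baseline.
- Table 3 itself is not shown. Its third footnote, on a limited telephone check of medication, names no arm, whereas the first two footnotes name group A. A contact in B before month 24 therefore cannot be fully excluded.

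On the text available, an SAE-triggered stop can come before the endpoint essentially only in A.

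**2. Inputs for size (Sample size section).** Decline in B 0.21; target 50% of it, so 0.5 × 0.21 = 0.105; SD 0.5; two-sided 5%; power 90%; inflation factor 1.1; dropout 10%; 576 per group.

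Reproducing the plan's figure: n per group = 2 × 0.5² × (1.960 + 1.282)² / 0.105² ≈ 477, against the stated 475. Then 475 × 1.1 × 1.1 = 574.75, close to 576 (dividing by 0.9 in the last step gives 580.6). The stated sizes reproduce to within about 1%.

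**3. Shift in a completer comparison.** Let p be the excess share lost in A and d the amount by which those lost are worse in change than the rest. The full A mean equals the completers' mean minus p × d, so the completers overstate A by p × d. Take a shift of 10% of the target, 0.0105, as a yardstick:

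| Assumed deficit d | p = 0.0105 / d | Participants (p × 576) |
|---|---|---|
| 1 SD = 0.5 | 2.1% | 12.1 |
| 0.5 SD = 0.25 | 4.2% | 24.2 |
| planned effect = 0.105 | 10% | 57.6 |

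Counted against the 518.4 per arm left after 10% dropout (576 × 0.9), the numbers are 10.9, 21.8 and 51.8.

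**4. What a shift of 0.0105 means.** SE of the difference = √(2 × 0.25 × 1.1 / 518.4) = 0.0326. The shift is 0.0105 / 0.0326 = 0.32 SE. With no true effect, the chance of a significant result in favour of A becomes P(Z > 1.96 − 0.32) = 0.051 instead of 0.025.

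**5. Power.** For the two-sided t-test with variances inflated by 1.1, 518.4 against 518.4 completers gives 0.896. Removing 12, 24 or 58 from A gives 0.893, 0.889 or 0.878.

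**The case against.** The strongest objection is that the text allows a harmless reading. Data collection plans the 24-month interview for everyone and makes no exception for people who have been stopped. Limitations uses the word participation for carrying out the programme: "Participation in our prevention trial is rather demanding since the intervention components address various lifestyle factors". An interruption need not end follow-up, and the coordinating center takes part in every decision, which limits variation between sites. A journal article also condenses the full protocol, where the handling of stopped participants may be spelled out. All of this stands as a limit on the point. It does not remove it, because the article states the rule itself, and the words it chooses, taken literally, end follow-up.

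The second objection concerns size. The article gives no SAE or stop rate, and Data monitoring rates the trial's risk as low. The deficits in the table are assumptions. The case of 58 excess losses equals the whole 10% dropout allowance and comes on top of it. The planned analysis is not a bare completer comparison: it includes inspection of missingness, growth models and weighting, and a dropout analysis would help to reveal such loss, though not prevent it. This stands too. The numbers are thresholds, not forecasts.

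A reader might infer more: that follow-up will be stopped after SAEs, that sites will apply the rule differently, or that group B is certain to have no contact before month 24. The documents support none of these.

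**Conclusion.** The point holds as a wording defect worth correcting, not as evidence of a biased trial. The stop after an SAE is fixed in terms that, read literally, end outcome follow-up. In the contact schedule described, the resulting endpoint loss would fall mainly on A and would favour A if those removed decline more.

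The size is unknown and probably small. It would take about 12 to 58 excess losses in A, depending on the assumed deficit, to move an unadjusted completer comparison by a tenth of the planned difference. Power is hardly affected; the issue is selective loss in one arm. The conclusion rests on three assumptions: the option is applied literally in at least some cases, those removed differ in cognitive course, and there is no undescribed contact in B. It concerns loss triggered by SAEs, not dropout in general.

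**What to change.** In Harms, change the option to *interruption or discontinuation of the assigned intervention (A or B) or of single components*. Add that the participant stays in follow-up, including adverse-event contacts where acceptable to them, and is invited to the 24-month assessment unless consent is withdrawn or the assessment itself is judged medically unsuitable, with the reason recorded. The decision to stop stays with the coordinating center and the site's principal investigator.

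The cost is a changed phrase, an added sentence and one extra field on the SAE form (intervention stopped, consent withdrawn, or assessment unsuitable, with reason). The downside is 24-month visits to a few participants who have stopped the intervention; these visits are already planned for all participants.

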### Auditing

Auditing will take place in form of reviews of the data collection across key assessment waves for each recruitment center. Specifically, 2 % of the questionnaires at baseline, at the face-to-face interim assessment (for intervention group A only), and at follow-up, respectively, will be randomly drawn and inspected regarding their degree of matching with the database input. Source data verification will be performed independently from investigators by the Hannover Medical School that is the entrusted site performing all data management tasks throughout the whole trial.

### Protocol amendments

Possible modifications to the protocol will be tracked in the German Clinical Trials Register (DRKS, registry number: DRKS00013555).

### Dissemination policy

*AgeWell.de* results will be published in scientific international, peer-reviewed journals, if possible with open access. Moreover, results will be presented at national and international scientific conferences as well as during seminars for GPs, regional care networks, and public events for seniors. Furthermore, publication results will be disseminated to the wider research community via press releases.

### Organizational structure and responsibilities

The Institute for Social Medicine, Occupational Health and Public Health (ISAP) in Leipzig acts as the coordinating center in *AgeWell.de*. This implies the organization of regular telephone-conferences and meetings with all participating centers, the compensation of all participating GP practices, preparation of documents needed for the conduct of the trial as well as reports to the funder of the study. Moreover, the study center in Leipzig also acts as one of the recruiting centers. As a subcontractor, the Institute for General Practice at the Hannover Medical School acts as the responsible study site for the task of data management, including the setup of the internet-based remote data capture system. The study centers in Greifswald, Kiel and Munich/Halle act as further recruiting study sites. Evaluation of cost-effectiveness of the trial will be conducted by the Department of Health Economics and Health Service Research at the University Medical Center Hamburg-Eppendorf. The intervention component “optimization of medication” will be realized by the Department of Clinical Pharmacology and Pharmacoepidemiology at the University Hospital Heidelberg, including the programming of algorithms to evaluate electronic data for optimization of medication and provision of documents for corresponding feedback to and from the GP.

## Discussion

Multi-domain interventions targeting lifestyle factors have been pointed out as a promising prevention strategy against dementia in international trials [5]. *AgeWell.de* will be the first such multi-component trial in older adults in Germany. We hypothesize that the multi-component intervention will be superior to general health advice and GPTAU in maintaining cognitive functioning in older adults at risk for dementia (primary hypothesis). Moreover, we assume beneficial effects in reducing mortality, nursing home placement, depressive symptoms, and in maintaining quality of life as well as functioning in everyday life (secondary hypotheses). Subsequently, this should also reduce direct health costs.

The *AgeWell.de*-study will add valuable insights regarding the role of modifiable risk and lifestyle factors to prevent or delay cognitive decline. A specifically useful asset should be findings from the intervention components that address potentially inappropriate medication [13, 26] and depression [8, 9, 69], which, to our knowledge, have not been examined in comparable RCTs so far.

Beyond that, our intervention will possibly also reduce risk for other diseases such as hypertension, stroke, cardiovascular disease, overweight etc. by addressing common risk factors for the respective diseases [2].

### Limitations

Participation in our prevention trial is rather demanding since the intervention components address various lifestyle factors and require e.g. cognitive training and physical activity on several days a week. The follow-up period is longer than in most previous trials testing single interventions. Therefore, adherence to the intervention might be lower compared to trials targeting only single components for a shorter time period. These factors also raise the chance of dropping out. We will address these potential problems by putting a strong focus on continuous motivation of participants and monitoring of adherence to the intervention, e.g. by regular telephone contacts and the use of motivational interviewing techniques. For ethical reasons, general health advice and feedback on known risk factors for dementia will also be provided to intervention group B. On these grounds, estimates of the effects of our intervention should be considered to be conservative.

### Outlook

Since the domains of our multi-component intervention address behaviors common in the general population, the intervention, if effective, will be implemented in real world settings. Thereby, *AgeWell.de* could add to targeted and cost-effective strategies in preventing dementia in older adults at risk. Most interventions tested (e.g. physical activity and a wholesome diet) are easily available to the majority of older adults [70]. Likewise, *AgeWell.de* addresses lifestyle factors that are common in general practice. Therefore, even a moderate decrease in exposure to the targeted lifestyle factors could lead to a significant reduction in incident dementia cases on a population level [5, 70]. Concerning the projected increase in number of dementia cases due to ageing populations, there is an evident need for effective prevention strategies. This becomes particularly relevant in regard to the absence of effective treatment options. To date, lifestyle interventions might constitute the most cost-effective and sustainable option for dementia prevention [71]. Against this background, the results of *AgeWell.de* will make a highly relevant contribution to the growing body of knowledge on modifiable risk factors for dementia.

## Data Availability

After publication of the final *AgeWell.de* trial results, electronic research data will be made accessible free of charge for third parties/further interested researchers upon request from the central data management center (work group Medical Statistics and IT-infrastructure at the Institute for General Practice, Hannover Medical School).

## Abbreviations

AD: Alzheimer’s disease
ADL: Activities of daily living
AE: Adverse event
BMBF: Bundesministerium für Bildung und Forschung (German Federal Ministry for Education and Research)
CAIDE score: “Cardiovascular Risk Factors, Aging, and Incidence of Dementia” Dementia Risk Score
CERAD: Consortium to Establish a Registry for Alzheimer’s Disease
DSM-5: Diagnostic and statistical manual of mental disorders, 5th edition
FINGER: Finnish Geriatric Intervention Study to Prevent Cognitive Impairment and Disability
GCP: Good clinical practice
GHA: General health advice
GP: General practitioner
GPTAU: General practitioner treatment as usual
IADL: Instrumental activities of daily living
ICER: Incremental cost-effectiveness ratios
LGM: Latent growth curve modeling
MoCA: Montreal Cognitive Assessment
NTB: Neuropsychological test battery
PI: Principal investigator
PIM: Potentially inappropriate medication
RCT: Randomized controlled trial
SAE: Serious adverse event
SD: Standard deviation
